#### Adherence

Adherence will be measured in a number of ways (outlined in detail, table 4):

**Table 4 T4:** Adherence measures

	What	How/additional validation
Self-report through my activity programme and control arm smartphone app	Exercises reported on app to their prescribed programme the day they are carried out. Exercise type Intensity Dose Adherence defined as participant carrying out 80% of their prescribed programme.	The health professional will be asked to provide a copy of the participants prescribed exercise plan, any changes to it and the dates any changes were made (both sites record this as part of standard intervention). For face to face home delivery, the health professional will be asked to report exactly what the patient has done when with them (this will be used to validate the self-report from participants). After discharge from rehabilitation if participants move onto other strength and balance provision. Those services will give us copies of the exercise programme delivered for any days the participants attend, attendance records and any prescribed home exercise programme.
EARS	Validated 16-question tool with a 6-question subscale specifically measuring adherence.	Paper questionnaire at baseline, 3 months and 6 months.

EARS, Exercise Adherence Rating Scale.

Self-report app will be used for both control and intervention groups. Adherence will be classed as the participant carrying out 80% of their prescribed programme (based on the evidence base for effective strength and balance).^6 38^
Exercise Adherence Rating Scale (EARS).^39^ This is a validated 16-question tool with a 6-question subscale specifically measuring adherence (remaining questions measure reasons for adherence/non-adherence).

##### Health economics

The health-related quality of life measures will include the European Quality of Life 5 Dimensions (EQ-5D-5L)^40^ and an additional measure used in previous trials related to falls prevention (the ICEpop CAPability measure for Older people (ICE-CAP-O).^41 42^ Costs of delivering the intervention will be observed based on staff training, delivery costs and equipment costs. Additional resource use measures will be captured via a Resource Use Questionnaire which will seek to measure costs related to an NHS and social care perspective (secondary, primary, community care service use), and a patient perspective (costs related to informal care). The findings from these will inform the feasibility of collection of the data, and priorities for cost collection at full trial.

#### Interviews/focus groups

The interview and focus group schedules are based on FARSEEING guidelines.^43^ The following key areas will be explored in relation to the smartphone, the ‘Motivate me’ app, ‘My activity programme’ app, FallsMonitor@home and the mTUG. Ease of use, clarity of screen, demonstration of use, wearing comfort, adaption of use, reliability, choice and control and home and lifestyle. This feedback will be considered and any required changes to the technology set-up, applications and intervention will be made prior to the definitive RCT. We also ask additional questions about the research process including general expectations and views; experiences of recruiting patients (health professional), and of being recruited and randomised (patients), suggestions of methods for recruiting participants; likely uptake and retention of participants.

### Analysis

Quantitative data are analysed using SPSS Release V.22.0. The main analyses is descriptive, involving the estimation of recruitment rates, attrition rates, non-compliance rates, means and SD of outcomes by group at baseline and end trial, and 95% CI for differences of means of outcomes between groups and assessment of change following the intervention at end trial. The health economics analysis is focused on informing relevant measures and means of collection of health-related quality of life and resource use for the future definitive study. Only an exploratory cost-effectiveness analysis will be conducted; for all measures we will report mean values and sample variability alongside information on missing values.

Data from the smartphone-based outcome measures (FallsMonitor@home, mTUG, My activity programme/control self-report app) will be compared with the traditional measures (falls calendar,^32^ TUG,^25^ EARS^39^) alongside qualitative feedback as part of their validation. A statistical analysis plan will be created before data analysis.

Qualitative interviews/focus groups will be analysed using thematic analysis.^44^ The research will be inductive and although will seek to further understand the quantitative findings, this approach will also generate categories and explanations directly from the data rather than based on previously set aims and objectives, reducing risk of bias.^44^ QSR International's NVivo V.10 qualitative data analysis software will be used to manage the data. The validity of the analysis will be checked by returning to the data once themes have been identified and also through the use of a second researcher who will check samples of analysis. The accuracy of the transcripts will be checked through discussion with participants to establish if anything is not clear from the interviews/focus groups.

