#### Recruitment, consent, sample size

Health professionals give patients the study information sheet and inform them about the intervention. The health professionals then ask the patient if they are happy to be contacted by the researcher who demonstrates the technology either in the patient’s home or within groups at each NHS site. The technology is demonstrated to the participant before they are asked to give informed consent. Where possible a former patient who has used the smartphone applications accompanies the researcher to demonstrate the technology. We think involvement of a peer has the potential to assist in promoting patient confidence in the use of the technology.

The first 36 eligible patients identified through each service (n=72 in total) who are willing to participate are being recruited and randomised (figure 1). Thirty patients per arm after attrition (approx. 10%) are normally used for feasibility RCTs.^26^ Study participants are randomised using a computer-generated randomisation algorithm at sealedenvelope.com, stratified by gender and site, using block randomisation (2, 4, 6 blocks) into either intervention or control group. Stratification is by gender and site to ensure equal distribution across sites as we are testing all trial procedures.

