#### Outcome measures

##### Falls

The primary outcome for any future definitive trial would be falls, expressed as fall rate per person per months of follow-up observation after randomisation. This study collects falls data for the purposes of testing feasibility of data collection, and to inform us of falls rates and intervention effect size for a future sample size calculation.

All participants will wear the smartphone in their pocket or on a waistband and this will act as a falls detector, running the FallsMonitor@home app developed by the University of Bologna.^10^ If the patient chooses then they can also use the app on the phone as a falls alarm. The fall detection system application allows the user to identify a list of formal/informal caregivers who will receive an SMS if a fall is detected. Patients are given an opportunity to de-active the falls alarm through an application on the smartphone if there is a false alarm, enabling the user to maintain control and prevent unwanted intrusion. Participants are asked if we can use their anonymised falls data for further development of the app and in the FARSEEING real-world falls database.^30^

To validate this as an outcome measure we use the internationally agreed Prevention of Falls Network Europe (ProFaNE) falls definition^31^ and follow the agreed ProFaNE falls data collection and analysis protocols based on self-report calendars.^32^

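### The only between-arm summary named is a difference of means plus change, with no baseline or stratum adjustment and no falls rate contrast, though the trial is to supply effect sizes for the definitive trial

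*Protocol article*

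**What the plan says.** The Analysis section sets out a descriptive plan: "The main analyses is descriptive, involving the estimation of recruitment rates, attrition rates, non-compliance rates". It continues with "means and SD of outcomes by group at baseline and end trial" and then the between-arm part, "95% CI for differences of means of outcomes between groups and assessment of change following the intervention at end trial". The section names no covariate, stratification term, rate or rate ratio. It adds: "A statistical analysis plan will be created before data analysis".

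Four other parts of the article bear on this:

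- **Recruitment, consent, sample size:** allocation is "stratified by gender and site, using block randomisation (2, 4, 6 blocks) into either intervention or control group". The stated reason is "Stratification is by gender and site to ensure equal distribution across sites as we are testing all trial procedures".
- **Blinding, and Table 3:** the physical tests and questionnaires are done at baseline, before randomisation.
- **Falls:** falls would be the primary outcome of a definitive trial, "expressed as fall rate per person per months of follow-up observation after randomisation". The falls data of the present trial are to inform falls rates and an effect size for a future sample size. The section also commits to the ProFaNE protocols for collecting and analysing falls.
- **Primary outcome measures, and Balance:** effect sizes are to be determined for sample-size calculations on the reduction in falls, and Berg effect sizes will enter the power calculation of the full trial.

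**The concern.** One stated product of this feasibility trial is a set of planning figures for a larger trial. The one between-arm summary that the Analysis section names is not the most useful source of them.

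For Berg, TUG, chair stand, Short FES-I, EQ-5D-5L and ICECAP-O, a pre-randomisation value is available for each participant assessed. A difference of end-of-trial means does not use it. A change score uses it with a fixed coefficient of one, which is inefficient unless the correlation is high. Neither reports directly the residual SD, which is what the sample size of a baseline-adjusted definitive analysis needs.

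For falls, a mean and SD at baseline and end of trial do not suit a count that accumulates after randomisation. Follow-up time will differ between people, since data up to withdrawal are kept (Patient withdrawal) and about 10% attrition is expected. Planning on falls needs a control rate, a rate ratio and a dispersion estimate, and the Analysis section promises none of these.

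**Working it through.** **Inputs from the article.** Target 72; 30 per arm after attrition of about 10%; assessments at baseline, 3 and 6 months.

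**Inputs that the article does not give.** The SD of any outcome, the baseline-to-6-month correlation r, the falls rate and its dispersion. Half-widths are therefore in SD units, and the rest are assumed ranges.

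**Sample size.** 60 / 0.9 = 66.7, so 67 would be enough for 30 per arm. With 72, 72 × 0.9 = 64.8, about 32 per arm. The target is on the safe side and the point does not depend on it.

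**Continuous outcomes, n = 30 per arm, 95% CI half-width.**

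- End-of-trial values only: t(58) × √(2/30) = 2.002 × 0.258 = 0.517 SD.
- Baseline-adjusted (ANCOVA): t(57) × √(2/30) × √(1 − r²).
- Change score: t(58) × √(2/30) × √(2(1 − r)).

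| r (assumed) | End only | Change score | ANCOVA | ANCOVA / end only | ANCOVA / change |
|---|---|---|---|---|---|
| 0.3 | 0.517 | 0.612 | 0.493 | 0.95 | 0.81 |
| 0.5 | 0.517 | 0.517 | 0.448 | 0.87 | 0.87 |
| 0.7 | 0.517 | 0.400 | 0.369 | 0.71 | 0.92 |
| 0.8 | 0.517 | 0.327 | 0.310 | 0.60 | 0.95 |

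For r from 0.5 to 0.8, ANCOVA intervals are 13% to 40% narrower than end-only intervals. In numbers of patients, the factor 1/(1 − r²) runs from 1/0.75 = 1.33 to 1/0.36 = 2.78. A change score is worse than end-only values at r = 0.3, equal at 0.5, and wider than ANCOVA in every row. At 32 per arm the half-widths are slightly smaller (0.500 SD for end-only values) and the ratios are the same.

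**Strata.** Adding site and gender uses two more degrees of freedom and changes the ANCOVA half-width by no more than 0.001 SD. Any gain depends on how far site and gender predict outcome, and the documents give nothing from which to work that out.

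**Falls.** For a negative binomial rate ratio with mean count μ = rate × 0.5 years and dispersion k, SE(log RR) = √(2(1/μ + k)/30), and the 95% CI runs from the estimate divided by to multiplied by exp(1.96 × SE). At 1.0 fall per person-year and k = 1: μ = 0.5, SE = √(2 × 3/30) = 0.447, factor 2.40. Over assumed rates of 0.5 to 1.5 per person-year and k of 0.5 to 2, the factor runs from 1.98 to 3.45. The rate ratio is on the right scale for planning but will be very imprecise.

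**The case against.** The strongest reply is that this rests on silence. The trial is an exploratory feasibility study, its analysis is descriptive, and a separate analysis plan is promised. Covariates and count models are normally left to such a plan, and a covariate-adjusted contrast is also a difference of means. All of that stands. It rules out calling the omission an error. It does not remove the value of settling the point, because the article does name a between-arm summary and asks the trial for effect sizes.

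A reader might go further in three ways, none of which the article supports:

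- **That baseline data are ignored.** The Analysis sentence summarises outcomes at baseline by group and includes change. If the SD of change is reported alongside the baseline and end-of-trial SDs, the correlation and hence a residual SD can be recovered. At high correlation a change score loses little.
- **That the plan contradicts itself on falls by analysing a rate as a mean.** The Analysis section uses only the general word for outcomes. The Falls section gives a rate scale, though worded for the definitive trial, says that the present data inform falls rates, and adopts the ProFaNE analysis protocols.
- **That intervals are wrong because the strata are left out.** An interval that omits the strata is conservative only if they are prognostic, which is unknown. Site is not overlooked either: the Primary outcome measures section plans to explore differing delivery length across sites.

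**Conclusion.** The point holds as a matter of precision and of fitness for planning the definitive trial. Read literally, the Analysis section names differences of means and change as its only between-arm summaries, without adjustment and without a falls rate contrast. Because the arms are randomised, such a contrast is valid, and its interval already allows for chance baseline imbalance. It should not be read as biased.

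The size rests on the assumed correlation. Over 0.5 to 0.8, adjustment narrows the interval by 13% to 40% against end-of-trial values alone, but by only 13% to 5% against a change score. The benefit from the strata cannot be quantified. For falls, the gain is an estimate on the scale that the article itself wants for planning. It is not a precise one: on the assumed rates and dispersions, the interval spans a factor of about 2 to 3.5 either side of the estimate.

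**What to change.** Keep means and SDs by arm as description. Add to the Analysis section, or to the analysis plan still to be written:

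1. Between-arm differences in continuous outcomes are estimated with 95% CI from a linear model containing arm, the baseline value of the outcome, site and gender. The residual SD is reported.
2. Calendar falls are summarised as rates per person-time, in line with the Falls section, with a rate ratio and 95% CI (for example from a negative binomial model with log follow-up time as offset). The control rate and dispersion are reported, with a note that the interval will be wide.
3. All of these remain descriptive, without hypothesis tests.

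The cost is wording and standard models. No new data, assessments or participants are needed, and the two stratum terms cost two degrees of freedom. The change should be made before data analysis begins.

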### Ethical issues

Regional and site-specific approvals have been obtained. We are collecting and storing personal information in accordance with the General Data Protection Regulation and Data Protection Act 2018. As this is a study with older patients a number of ethical issues could arise. To address these, community services will act as gatekeepers to access patients and assess patients’ eligibility for the study. The intervention is delivered by health service staff and provided in addition to standard service; therefore patients are unlikely to be disadvantaged.

If falls are detected by the smartphone, it is important that someone is informed in real time. The smartphone application allows the user to select a list of formal/informal caregivers who will receive an SMS if a fall is detected. It will be made clear that the falls service is not an emergency service so in the event of a fall the person receiving the text message would call an ambulance as they would in normal circumstances. If patients already wear a call alarm then they will be encouraged to continue to use this as well or to adopt their usual method of alerting help.

The study requires monitoring of subjects and it is important that patients do not find this obtrusive (privacy issues have been identified as major barriers to the use of technology). Patients are given an opportunity to de-active the falls alarm through an application on the smartphone if there is a false alarm. However, previous consultation/usability testing with older adults raised no major privacy issues.

There are ethical issues in the removal of technology at the end of studies.^45^ We will not be able to offer older adults the technology at the end of the 6-month study period, but they will be offered the opportunity to download the apps onto their own phones if they wish.

The risk of interviews and focus groups are minimal. The patient or health professional can ask the researcher to move onto another question if they are uncomfortable at any point. Health professionals will be given the chance to discuss the trial, technology and intervention in a one-to-one interview if they do not feel comfortable giving feedback in front of colleagues.

### Patient and public involvement

Patient and public representatives have been involved in designing the trial including outcome measures. Feedback from previous usability testing with patients and from patients who sit on our Advisory Group (AG) provided direct information on the design of the trial for example, use of self-report app for control arm. Patients on our AG (who were formerly patients of one of the services) helped to design study material such as the patient information sheet. They assisted in training health professionals in approaching patients for recruitment and goal setting as part of the intervention. Three participants, who took part in our usability testing, became peer mentor volunteers for the trial. They will attend the first visit (if the patient gives permission) to demonstrate the technology to patients before consent is given. We will explore whether peer involvement aids recruitment. Finally, the volunteers and the patients who sit on our AG will aid with dissemination of study findings, for example helping to arrange dissemination events and providing feedback on newsletters for participants.

### Trial monitoring

The lead researcher ([name]) will monitor the delivery of the intervention and recruitment of patients; there will also be a clinical lead ([name]) at each site taking overall responsibility for identification of patients and delivery of the intervention. This team, alongside academic experts ([name]) from the Trial Co-ordination Group will ensure overall quality of trial data. The AG meets bi-annually, giving feedback on the project, providing expert guidance and assisting in dissemination; this includes two previous patients. A risk register is reviewed by the AG. The study is subject to the audit and monitoring regime of the University of Manchester and the monitoring plan followed.

A detailed risk assessment has been carried out and potential patient, organisational and study hazards considered, the likelihood of their occurrence and the resulting impact should they occur.

## Adverse events

A safety reporting protocol has been developed for related and unexpected serious adverse events (AEs) and directly attributable AEs. An AE is defined as any untoward medical occurrence in a subject which does not necessarily have a causal relationship with treatment. These AEs are recorded in the CRF and if a serious AE occurs then it is reported to the chief investigator (CI). The CI will determine whether AEs require reporting to the trial sponsor and ethics committee, in accordance with the safety reporting protocol.

## Discussion

This is the first trial that we are aware of that explores the potential use of motivational smartphone apps for the support of an evidence-based falls exercise programme.

As this is an active intervention and control we are unable to blind participants or those delivering the intervention. However, the design does enable us to blind those carrying out both the assessments and analysis. The fact that both arms have a smartphone minimises the risk of unblinding with the independent assessors and, we would argue, also reduces risk of drop-out. There is the potential for the control group to become motivated by reporting their activities. However, if we did not ask them to report, there is also the risk of any difference between groups being a function of differential reporting schedules rather than a function of the intervention per se.

We provide participants with study phones, which may be different to using the app on their own phones. However, we need to ensure the smartphone meets the technical specification required for FallsMonitor@home to work correctly. Furthermore use of study phones enables us to maintain confidentiality of participants (if phones are lost we can wipe them remotely).

This trial assesses several novel outcome measures against the gold standard, the mTUG against standard TUG, the FallsMonitor@home against standard calendar method and a self-report app against the EARS tool.^39^ This enables us to further our understanding of whether technology has the potential to provide more objective and reliable outcome measures than current methods.

We use two very different NHS sites, reflecting the reality of day-to-day practice (one specialist falls service, one general rehabilitation services) to explore the delivery of the intervention. This means that the standard service is different across the two sites adding complexity to how the control and intervention arm are delivered. However, these differences enable us to assess its scalability to full trial where different types of falls services would need to be included as sites. It also enables us to be more representative of current services and assess its potential for delivery in practice.
